### Sample size

This study employs three groups with a 1:1:1 ratio. The primary research indicator is HbA1c, where *α*=0.05, *β*=0.2, and considering a 20% dropout rate, the minimum sample size for a single group is 100 cases. Therefore, a total of at least 300 cases should be included in the three groups.

### Recruitment

We will recruit patients at the First People’s Hospital of Kunshan in Jiangsu Province, China. Once recruited, the study staff will guide patients through the process of learning digital intervention operations/diary card recording, and confirm the content and frequency of digital intervention and the requirements for diary card recording with the patients.

### Sequence generation

In this randomized controlled trial, a simple randomization method was used to allocate participants to three groups with a 1:1:1 allocation ratio. Group A: digital intervention + virtual incentives + conventional treatment, Group B: digital intervention + physical incentives + conventional treatment, and Group C: conventional treatment. A central randomization system for the EDC clinical trial is established and implemented. Randomizers at the trial center will access the system with an account number and password, enter basic information about the subject patients and generate a randomization number for follow-up.

### Concealment mechanism

Allocation concealment will be ensured by the following mechanism. Staff will log into the EDC Trial Data Cloud and enter information for participants. The EDC trial data system will randomly assign participants to any group in a 1:1:1 ratio. Once the necessary baseline information has been entered, a patient summary will be generated. To evaluate the data, an account and password will be required.

### Implementation

The allocation sequence is generated by the EDC centralized randomization system. The research assistant will be responsible for patient registration. The Trial Management Committee (TMC) will assign interventions to participants.

### Assignment of interventions

Participants and investigators will be informed about the interventions assigned to them in this open-label trial. Due to the nature of the patient-reported outcome indicators, not all outcome evaluations will be blinded. Assignment will not be known to statisticians during the analysis. As this is an open-label trial, no blind-breaking procedures will apply.

### Data collection

Data will be collected at the study site using EDC. Data will be collected at a total of 5 time points: baseline, intervention period day 1, day 28±5, day 56±5 and day 84±5. The data collected will be stored in the form of an electronic CRF. Investigators will be informed of any changes made by the CRC and the system will automatically perform a system/edit check. Authorized investigators will be given access to the study computer and will evaluate the data throughout the course of the study. If any missing data is detected through the EDC system, the investigator will contact the participant by telephone.

### Data management

Internal monitoring includes monitoring of appropriate informed consent documentation/records, eligibility criteria, data quality, etc. Monitoring is usually carried out by relevant parties involved in the study to identify problems and improve the process. When data is analyzed, a unique identifier is generated to ensure the security of the data. Information on incorrect or missing data is sent to the Data Manager (DM) in the Data Query Report. The DM who receives the review will check the original records to identify corrections. The original documents and signed informed consent forms will be stored in a locked filing cabinet.

### Confidentiality

Personal information will be collected, shared and maintained in accordance with the International Conference on Harmonisation Good Clinical Practice Guidelines (ICH GCP).

### Statistical methods

All data will be entered separately by 2 members and analyzed after confirming complete agreement of data. SPSS 22.0 will be used for statistical analysis. All measures will be tested for normality using the Shapiro-Wilk method, and data that conform to a normal distribution will be statistically described using the mean ± standard deviation; data that do not conform to a normal distribution will be statistically described using the median (P25, P75), and correlation will be analyzed by Pearson correlation analysis, with differences considered statistically significant at P<0.05. Statistical descriptions of the different groups will be made using the mean, standard deviation, median, minimum, and maximum values for the different groups of measures. Statistical description of the count data of the different groups will be made using frequency (composition ratio). Changes before and after the intervention in each group will be calculated using exact probability or non-parametric tests. The analysis of dropout will statistically describe the actual number of subjects enrolled, the number of dropouts, and the number of dropouts one by one and analyze the specific reasons for dropout and dropout. Analysis of the balance of underlying values will use ANOVA or exact probability calculations to compare demographic information with other indicators of underlying values to measure the extent to which each group is in balance.

All patients who have received the behavioral economics-based digital intervention for at least 4 weeks will be included in the full analysis set (FAS). Depending on the timing of the survey, the analysis set following the study protocol (per-protocol, PP) will consist of patients who have completed a 3-month follow-up examination. The FAS will be used as the basis for the preliminary analysis. If the difference between the FAS and PP samples is greater than 10%, the analysis will be repeated for the PP analysis set. The safety population includes patients with FAS. Unless otherwise stated, all analyses will be performed on both the FAS and PP analysis sets. No additional analyses will be performed.

Missing values will not be replaced or added. All analyses will be based solely on observed cases. Patients lost to follow-up will be considered to have dropped out of treatment. Only PP patients will be used in sensitivity analyses to test the impact of this assumption. No genetic or molecular analysis will be performed in this trial or future use.

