**Methods:**

This trial is a prospective randomized controlled trial conducted at the First People’s Hospital of Kunshan City from April 1, 2023, to December 31, 2024, with a follow-up period of 3 months. The specific randomization method was established and implemented through the EDC clinical trial center’s randomization system. We will measure and collect baseline data from three groups, including Group A: digital intervention + virtual incentives + conventional treatment, Group B: digital intervention + physical incentives + conventional treatment, and Group C: conventional treatment. HbA1c, weight, SMBG testing rate, diabetes self-efficacy, and diabetes-related medical expenses will be recorded at baseline, 1 month, 2 months, and 3 months for all three groups. The Shapiro-Wilk test will be used to test for normality, and Pearson correlation analysis will be used for correlation analysis. Dropouts will be analyzed separately. Analysis of variance or exact probability calculation will be used to compare demographic data and other baseline indicators.

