## Materials and methods

### Objectives

Aim1: To assess the effect of behaviorally informed digital intervention on HbA1c levels, prevalence of SMBG detection, weight, diabetes self-efficacy, and diabetes-related expenses in patients with type 2 diabetes compared to standard treatment.

Hypothesis 1a: Evaluate the changes in HbA1c levels in the intervention and control groups. At 3 months, there will be significant differences in HbA1c levels prevalence of SMBG detection, weight, diabetes self-efficacy, and diabetes-related expenses among the three groups: A (digital intervention + virtual incentives + standard treatment), B (digital intervention + tangible incentives + standard treatment), and C (standard treatment).

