### Study design and setting

This study is a single-center, randomized, controlled, open-label, parallel-group superiority trial. Patients were randomly assigned in a 1:1:1 ratio to evaluate the efficacy of behavioral economics-based digital intervention on HbA1c, SMBG testing rate, and diabetes self-efficacy in patients with T2DM. The study protocol followed the Standard Protocol Items: Recommendations for Interventional Trials (SPIRIT) guidelines [19]. This study will be conducted at the First People’s Hospital of Kunshan City, Jiangsu Province, China, from April 1, 2023 to December 31, 2024.

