### Outcomes

#### Primary outcome measures

The primary endpoint is to compare the difference in HbA1c levels among the three groups at the 3-month follow-up. After enrollment, the HbA1c levels will be recorded at baseline and at the end of the first, second, and third digital intervention cycles.

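### Read literally, the statistical methods fix only a within-arm before-after test for outcomes, so no stated test answers the between-arm primary question

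*Protocol article*

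**What the plan says.** The question is a comparison between arms. Under Primary outcome measures: "The primary endpoint is to compare the difference in HbA1c levels among the three groups at the 3-month follow-up". Hypothesis 1a, under Objectives, expects the same of arms A, B and C: "At 3 months, there will be significant differences in HbA1c levels". The design is a "single-center, randomized, controlled, open-label, parallel-group superiority trial".

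The Statistical methods section gives each procedure a purpose:

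- Shapiro-Wilk is for normality.
- Pearson correlation is for correlation. It is tied to no arm comparison.
- For outcomes over time: "Changes before and after the intervention in each group will be calculated using exact probability or non-parametric tests".
- For a comparison across arms: "Analysis of the balance of underlying values will use ANOVA or exact probability calculations to compare demographic information" and other baseline values. The Abstract has the same limit: "Analysis of variance or exact probability calculation will be used to compare demographic data and other baseline indicators".

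After the definitions of the analysis sets, the section closes with "No additional analyses will be performed". No part of the article names a test that compares HbA1c, or any other outcome, between arms.

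**The concern.** A before-after test inside one arm does not use the randomisation. It asks whether HbA1c moved in that arm, not whether it moved more than in another. Patients enter with HbA1c between 7.0% and 10.5% (Inclusion criteria), and every arm is treated and followed. Regression to the mean and trial attention could therefore lower HbA1c in all three arms, including C. One arm can then cross P<0.05 while another just misses, with no difference between them.

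Two things are at stake. A reader given three within-arm P values may take significance in A or B but not in C as evidence of efficacy. The trial would also have no prespecified test of its own primary hypothesis, although baseline and 3-month HbA1c are both collected and would support a precise one.

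**Working it through.** **1. Question and stated method, side by side.**

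| Purpose | Test named |
|---|---|
| 3-month HbA1c among A, B and C (primary) | none |
| Secondary outcomes among A, B and C | none |
| Change within each arm | exact or non-parametric |
| Baseline values among arms | ANOVA or exact |

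**2. Inputs.** From Sample size: 100 per arm, 20% dropout, α = 0.05, β = 0.2. Evaluable patients per arm: 100 × (1 − 0.2) = 80. The article gives no effect size, SD or sidedness, so the figure of 100 cannot be reproduced. Assumed here: two-sided α, SD of change 1.2 points, a fall common to all arms of 0 to 0.5 points, and a correlation r between baseline and 3 months of 0.3, 0.5 or 0.7.

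**3. How often the misleading pattern arises with identical arms.** Let p be the chance that one arm's before-after test is significant, from a paired t-test with noncentrality (fall / 1.2) × √80. Arms are independent, so

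P(A or B significant, C not) = [1 − (1 − p)²] × (1 − p).

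| Common fall (points) | p | Pattern |
|---|---|---|
| 0 | 0.050 | 9% |
| 0.1 | 0.114 | 19% |
| 0.2 | 0.313 | 36% |
| 0.3 | 0.598 | 34% |
| 0.4 | 0.838 | 16% |
| 0.5 | 0.957 | 4% |

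Example at 0.2: [1 − 0.687²] × 0.687 = 0.36. The expression cannot exceed 38.5%, reached at p = 0.42.

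The plan speaks of non-parametric tests, so the pattern was also simulated with the Wilcoxon signed-rank test (2,000 trials per setting, 80 per arm). For common falls of 0.1, 0.2 and 0.3 SD it occurred in 21%, 38% and 26% of trials at r = 0.5, and in 27%, 33% and 7% at r = 0.7. With no fall it occurred in about 10%. In the same simulations, including falls of up to 0.4 SD, the ANCOVA test of arm rejected in 4.4% to 5.4%.

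**4. What baseline adjustment gives.** With 80 per arm, a two-sample t-test on 3-month values has 80% power at 0.446 SD. ANCOVA reduces the residual SD by √(1 − r²), so the effective difference is 0.446 / √(1 − r²).

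| r | Effective difference | Power, α = 0.05 per contrast | Power, α/3 per contrast |
|---|---|---|---|
| 0.3 | 0.467 | 84% | 70% |
| 0.5 | 0.515 | 90% | 80% |
| 0.7 | 0.624 | 97.5% | 94% |

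The gain depends on the comparator. Against an unadjusted comparison of 3-month values, the sample-size equivalent is 1/(1 − r²) = 1.10, 1.33 or 1.96. Against a between-arm comparison of change scores it is 2(1 − r)/(1 − r²) = 2/(1 + r) = 1.54, 1.33 or 1.18.

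**The case against.** The strongest reply is that the article does commit to a comparison among the three arms, in Objectives, Primary outcome measures and Secondary outcome measures. What it lacks is the name of the test and its covariates, which a condensed article may leave to the full protocol or analysis plan. That stands in part: a missing covariate list alone would be no finding. But this article does more than omit. It gives each test a purpose, keeps the across-arm tests for baseline, gives outcomes a within-arm test and closes the list. An analysis plan with a between-arm primary test would have to depart from that text.

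The wording is also loose. Changes in each group could mean change scores later compared across arms, though the text does not say so. The closing sentence follows the analysis-set definitions and may be meant to rule out only extra analyses. Even on that reading, no between-arm outcome test is named.

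Four stronger readings are not supported:

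- A reader might infer that the sponsor plans to claim efficacy from within-arm significance. Nothing calls the before-after test the primary analysis or states such a rule.
- A reader might infer that about a third of null trials would mislead. That holds only for assumed common falls of about 0.2 to 0.3 points with the assumed SD; at the other falls examined it is 4% to 19%.
- A reader might infer that before-after tests throw baseline HbA1c away. A change score uses baseline, though less efficiently than ANCOVA.
- A reader might infer that adjustment gives up to twice the effective sample. The factor of 1.96 is against unadjusted 3-month values at r = 0.7; against change scores it is 1.18.

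**Conclusion.** The point holds and should be corrected before analysis. The primary question is between arms, the only outcome test fixed is within arms, and the article does not bridge the two. This conclusion rests on the text and on no assumed figure.

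The size of the risk does rest on assumptions. The misleading pattern has a probability between about 4% and 36% over common falls of 0 to 0.5 points with an SD of change of 1.2, and none of these values is in the article. The power figures depend on the assumed correlations and on how α is shared among contrasts. With α/3 and r = 0.3, power is about 70%, so three contrasts are not free unless the multiplicity rule is chosen with that in view.

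**What to change.** In Statistical methods:

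1. State the primary analysis as ANCOVA of 3-month HbA1c on arm, with baseline HbA1c as covariate.
2. Specify either an overall test of arm or a multiplicity rule for A−C, B−C and A−B, and report the adjusted differences with 95% confidence intervals.
3. Label within-arm change as descriptive only.
4. Define the analysis set so that it includes arm C. The full analysis set is now limited to patients who had at least 4 weeks of the digital intervention, which read literally leaves C out. Without this change, naming the model would not give a valid A−C or B−C comparison.
5. Use the same model for self-efficacy, whose scale is scheduled at day 1. Use it for weight only once the Abstract, which has weight recorded at baseline, is reconciled with Table 1, which ticks weight only from day 28.
6. Reword the closing sentence so that it cannot be read as excluding these comparisons.

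For HbA1c the cost is wording: Table 1 already schedules it at baseline and day 84, and no more patients or data are needed. The multiplicity rule has a cost in power per contrast, shown above. Weight may need a baseline measurement if Table 1 reflects actual practice.

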### Interventions

To compare the effects of digital intervention based on behavioral economics theory on HbA1c, SMBG testing rate, and diabetes self-efficacy in patients with T2DM, conventional treatment was used as a control intervention. Conventional treatment was administered according to the T2DM conventional drug treatment method recommended by clinical guidelines. Conventional drugs include but not limited to metformin, sulfonylureas, glinides, α-glycosidase inhibitors, TZDS, DPP-4i, SGLT2i, GLP-1RA, and insulin. Digital intervention refers to the use of WeChat mini-program in smartphones to provide patients with out-of-hospital coordinated management based on cognitive behavioral therapy, guiding patients to improve their health behaviors in coping with diabetes and enhance the level of blood glucose self-management. The main content includes disease knowledge courses, auxiliary training courses (diabetic diet essentials), psychological counseling courses, course Q&A games, and relevant behavior records (daily attendance, medication check-ins, daily sugar control diet punch card). From day 1 to 1 month of the study is the first cycle, to 2 months is the second cycle and to 3 months is the third cycle.

After completing a single cycle of digital intervention, the subjects who receive digital intervention can receive virtual and tangible incentives respectively. On the first day of each cycle, the incentive content to be received at the end of the cycle will be reminded during follow-up. The subjects need to provide self-recorded and completed SMBG diaries to the researchers to receive incentives after check-in. The virtual incentive is a healthy behavior learning badge that lights up each cycle, including bronze, silver, and gold, which are awarded in turn according to the user’s completion (≥70%, ≥80%, ≥90%) judged by the researcher. The tangible incentive is a health behavior auxiliary tool provided each cycle, including an electronic medication box, a weight scale, and a smart bracelet, which are awarded in turn according to the user’s completion (≥70%, ≥80%, ≥90%) judged by the researcher.

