### Criteria for discontinuing or modifying allocated interventions

Participants will not be considered as having withdrawn from the study in the following cases, and they will be eligible for protocol evaluation unless they withdraw their consent for assessments:If the participant requests to discontinue the program treatment;If the participant is unable to continue the program treatment due to adverse events;When the researcher considers that the risks of continuing the program treatment outweigh the benefits for any reason; andFor any of the other reasons, the researcher deems it unsuitable to continue the program treatment.

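### The full analysis set is defined by four weeks of digital intervention, so on no reading does the main analysis compare all randomised patients

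*Protocol article*

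**What the plan says.** - **Full analysis set (FAS)** (Protocol article, Statistical methods): all "patients who have received the behavioral economics-based digital intervention for at least 4 weeks will be included in the full analysis set". No separate rule is given for the control arm.
- **Its role** (same section): "The FAS will be used as the basis for the preliminary analysis". The safety population is tied to the same set.
- **Per-protocol (PP) set** (same section): patients who completed the 3-month examination, with no condition on digital exposure. Analyses are to be run on both sets unless stated otherwise, and further analyses are ruled out. Missing values are not imputed; only observed cases are analysed.
- **Who gets the digital intervention**: Groups A and B. Sequence generation lists "Group C: conventional treatment", and Interventions says that "conventional treatment was used as a control intervention".
- **Primary endpoint** (Primary outcome measures): "The primary endpoint is to compare the difference in HbA1c levels among the three groups at the 3-month follow-up".
- **Patients who stop the programme**: "Participants will not be considered as having withdrawn from the study in the following cases, and they will be eligible for protocol evaluation" (section Criteria for discontinuing or modifying allocated interventions). The one exception is a patient who no longer consents to being assessed.

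**The concern.** The main analysis set of a randomised superiority trial is defined by something that happens after randomisation and that one of the three arms cannot experience. This is a rule the protocol states, not a detail left to an analysis plan.

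Two things are at stake. First, as worded, the named main set cannot support the comparison with conventional treatment, and control patients have no place in the safety population. Second, the obvious repair of keeping all of C leaves a filter that acts on A and B alone. If patients who stop a behavioural programme in the first month differ in HbA1c from those who continue, that filter alone produces a difference from C when the programme does nothing. No other set in the document covers all randomised patients, so nothing in the plan would show the problem.

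**Working it through.** **1. Who can enter the FAS.** Let q be the share of patients with less than four weeks of the relevant treatment, with 100 randomised per arm.

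| Reading | A | B | C |
|---|---|---|---|
| As worded | 100(1−q) | 100(1−q) | 0 |
| C kept whole | 100(1−q) | 100(1−q) | 100 |
| Four weeks of assigned treatment in every arm (not stated) | reduced | reduced | reduced by its own share |

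The first row needs no assumption for C. None of the three rows is the randomised population. The PP set can contain C, but it is also selected after randomisation. Because it lacks the four-week condition, it is not nested in the FAS.

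**2. The plan's own figure.** Sample size gives 100 per group from α = 0.05, β = 0.2 and 20% dropout, without an HbA1c difference or SD, so it cannot be reproduced forwards. Backwards, 80/(1 − 0.20) = 100, and 80 evaluable per arm implies a standardised difference of (1.960 + 0.842) × √(2/80) = 0.443 for a two-sided pairwise test. This serves only as a scale for the bias.

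**3. Bias if C is kept whole, with no true effect.** Assumed, because the documents give none of these: SD 1.2 points; q = 10% or 20%; early stoppers' 3-month HbA1c higher by D = 0.5 or 1.0 points; all of them attend day 84.

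- Arm C mean = μ + qD; filtered arm mean = μ; bias in favour of A or B = qD.
- SE = 1.2 × √(1/(100(1−q)) + 1/100): 0.174 for q = 0.1 and 0.180 for q = 0.2.
- Type I error of one pairwise test = P(|Z + qD/SE| > 1.96).

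| q | D | Bias qD (points) | qD/SE | Type I error |
|---|---|---|---|---|
| 0.1 | 0.5 | 0.05 | 0.29 | 0.059 |
| 0.1 | 1.0 | 0.10 | 0.57 | 0.088 |
| 0.2 | 0.5 | 0.10 | 0.56 | 0.086 |
| 0.2 | 1.0 | 0.20 | 1.11 | 0.199 |

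For scale, 0.443 SD is 0.443 × 1.2 = 0.53 points, so the bias runs from 0.05/0.53 = 9% to 0.20/0.53 = 38% of the difference that the sample size implies.

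**4. The three-group test.** The endpoint compares three groups, so the same null case was simulated for a one-way ANOVA (100 per arm, 6,000 replicates, A and B filtered, gap in SD units). With 20% removed and a 0.5 SD gap, the type I error is about 10%. Over 10% to 30% removed and gaps of 0.25 to 1.0 SD, it runs from about 5.4% to 47%.

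**5. What the rule adds when some early stoppers do not return.** Only observed cases are analysed, so a stopper without a 3-month HbA1c is absent under any FAS definition. If a share r of early stoppers attends, the rule shifts the observed arm mean by D × qr/(1 − q + qr). With r = 1 this is qD. With q = 0.2 and, for illustration, r = 0.5, it is D × 0.10/0.90 = 0.056 to 0.111 points, against 0.10 to 0.20 above. With r = 0 it is zero.

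**6. A versus B.** The same filter applies in both arms, so the bias in step 3 does not carry over to that comparison.

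**The case against.** - **A reader might infer that the trial cannot compare anyone with control.** The document does not support this. The PP set has no exposure condition, Group C completers belong to it, and analyses are planned on both sets. One sentence makes the PP repeat depend on a difference of more than 10% between the sets, but another plans it without that condition. What fails is the FAS comparison with C. This objection stands.
- **A reader might infer that the discontinuation section flatly contradicts the FAS rule.** That section most naturally concerns continued assessment, not membership of an analysis set, and someone who stops after week 4 satisfies both texts. There is tension only for those who stop earlier: they stay eligible for evaluation but drop out of the main set.
- **A reader might infer that the rule makes the programme look effective, or compares engaged users with all usual-care patients.** The direction depends on early stoppers having higher HbA1c, which nothing in the document shows. The rule sets a duration of receipt, not a threshold of use.
- **The authors may have meant four weeks of assigned treatment in every arm**, that is, reaching the end of the first cycle. This is plausible and would soften the asymmetry. The text does not say it, and patients would still be excluded on what happened after randomisation.
- **The text says preliminary, not primary.** True, but the FAS is the named basis of analysis and no all-randomised set is defined as an alternative.

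**Conclusion.** The FAS definition is wrong as written and should be changed. As worded, it leaves Group C out of both the FAS and the safety population; this follows from the text without any assumption. Under either more generous reading the set is still selected after randomisation.

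The size of the bias is conditional. With C kept whole and the assumptions in step 3, it is 0.05 to 0.20 HbA1c points in favour of A or B over C, with a type I error of about 6% to 20% for one pairwise test. These are upper values for the assumed stopping shares if some early stoppers miss day 84, and they would reverse in direction if early stoppers had lower HbA1c. The comparison with C survives in the PP set, but only among completers.

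**What to change.** 1. Define the FAS as every randomised participant, analysed in the allocated arm whatever the exposure to the mini-program, and name it as the primary analysis set.
2. Keep collecting day-84 HbA1c from those who stop the programme, as the discontinuation section already allows. Without this, observed-case analysis still loses them, and the new definition alone would not bring them back.
3. If a set with at least four weeks of exposure is of interest, report it as a labelled supplementary analysis. Do not add the condition to the PP set: applied to A and B only, it would bring the same one-sided filter into a set that now has none.
4. Define the safety population separately from the FAS, so that it includes Group C and those who stop before week 4.

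The cost is a change of wording before database lock, with no patients or visits beyond those planned. The downside is that the estimated effect may be slightly smaller.

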### Composition of the data monitoring committee, its role, and reporting structure

There will be no data monitoring committee for this study because the intervention in this study is considered a low-risk intervention.

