### Adverse event reporting and harms

Any adverse events that occurred between the time the subject signed the informed consent and was enrolled in the study and the end of the study, regardless of whether there was a causal relationship with the intervention. Any medical condition or clinically significant laboratory abnormality occurring prior to the administration of the intervention on day one is considered pre-existing and must be documented on the case report form. All AEs occurring after the administration of the intervention up to the last day of the study (including follow-up, the pause period of the study) must be recorded as AE subsets in the appropriate CRF section. When completing the adverse event form in the CRF, the investigator will use a scale of “1 to 5” to describe the severity of the adverse event. To standardize the criteria, the intensity of the adverse event will be judged by reference to the CTCAE v3.0 grading definitions: Grade 1 (mild, asymptomatic, or with mild signs; clinical or diagnostic observations only; no intervention required), Grade 2 (moderate, requiring minimal, local or non-invasive treatment, age-appropriate instrumental limitation of activities of daily living), Grade 3 (severe or clinically significant but not immediately life-threatening; hospitalization or prolonged hospitalization; disabling; limited ability to perform activities of daily living), Grade 4 (life-threatening, requiring urgent treatment), Grade 5 (death). The type and frequency of any adverse event will be reported to the Chinese National Adverse Reaction Monitoring Centre.

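### The safety population is set to the FAS, so patients who stop the digital intervention before 4 weeks, including for an adverse event, fall outside the safety analysis; read literally, so does Group C

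*Protocol article*

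**What the plan says.** Four parts of the protocol article bear on this point.

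- **Analysis sets (Statistical methods).** The FAS is defined by exposure: "All patients who have received the behavioral economics-based digital intervention for at least 4 weeks will be included in the full analysis set (FAS". The safety set is then tied to it: "The safety population includes patients with FAS". The same paragraph has analyses run on the FAS and per-protocol sets and rules out additional analyses. No other safety set is described.
- **Arms (Sequence generation; Interventions).** The third arm is "Group C: conventional treatment", and "conventional treatment was used as a control intervention". That arm does not receive the digital intervention.
- **Stopping the intervention (Criteria for discontinuing or modifying allocated interventions).** "Participants will not be considered as having withdrawn from the study in the following cases", and one of the listed cases is "If the participant is unable to continue the program treatment due to adverse events". Such patients stay eligible for evaluation unless they withdraw consent to assessments.
- **Adverse events (Adverse event reporting and harms).** The scope opens with "Any adverse events that occurred between the time the subject signed the informed consent and was enrolled in the study"; the window runs until the trial closes, whatever the cause. Conditions arising before day 1 are documented as pre-existing. Everything after the intervention starts, up to the last study day, goes into the case report form. No minimum exposure is set.

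**The concern.** The document collects adverse events from everyone from the first day, foresees that some patients will stop because of such events, and keeps those patients in the study. It then defines the set in which safety is analysed by a condition that these patients fail if they stop before 4 weeks. Membership of the safety set thus depends on having stayed on the intervention for a month, which is related to what a safety analysis is meant to examine. Both the patient and the patient's events leave the calculation.

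The literal wording has a second effect. Group C cannot satisfy a condition about receiving the digital intervention, so the safety set has no control arm. Events are counted regardless of cause and all arms receive glucose-lowering drugs, so a rate in A and B with no comparator cannot separate background events from effects of the intervention.

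At stake is whether the final safety tables describe the randomised patients or a selected subset. The efficacy conclusion is not affected by the safety set, and no safety measure is among the primary or secondary outcomes.

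**Working it through.** The point rests on definitions, and the protocol gives no safety figure to reproduce. The only planned numbers used are those under Sample size: 100 per group in three groups, 3 × 100 = 300. The protocol gives neither an early-stopping rate nor an adverse event rate, so every such rate below is an assumption.

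**1. Who is in the set.** Let e be the share of A and B (200 patients) that stops before 4 weeks.

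- Literal wording: size = 200 × (1 − e).
- Group C kept, 4-week rule applied to A and B only: size = 100 + 200 × (1 − e).

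| e (assumed) | Literal wording | Left out of 300 | Group C kept | Left out of 300 |
|---|---|---|---|---|
| 0% | 200 | 100 | 300 | 0 |
| 5% | 190 | 110 | 290 | 10 |
| 10% | 180 | 120 | 280 | 20 |
| 20% | 160 | 140 | 260 | 40 |

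On the literal wording at least 100/300 = 33% are outside the safety population. With Group C restored, only early stoppers are outside, but A and B are then selected arms set against an unselected one.

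**2. What this does to a rate within one digital arm.** Let r_stay and r_early be the event rates in patients who stay at least 4 weeks and in those who stop earlier. The safety set shows r_stay. The rate in the whole arm is (1 − e) × r_stay + e × r_early. The difference, whole arm minus safety set, is e × (r_early − r_stay).

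- *Stopping linked to events (assumed).* Of 100 patients, 10 stop early, 4 of them for an event, and 6 of the other 90 have an event. The safety set shows 6/90 = 6.7%; the whole arm has (6 + 4)/100 = 10%. Check: 0.10 × (0.400 − 0.067) = 0.033, an understatement of 3.3 points.
- *Stopping unrelated to harm (assumed).* The same 10 stop early with no events. The safety set still shows 6/90 = 6.7%; the whole arm has 6/100 = 6.0%, an overstatement of 0.7 points.

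**3. Sensitivity when events cause the stopping (assumed).** Suppose 10 of 100 patients in an arm have an event, a share s of those 10 stops before 4 weeks because of it, and nobody else stops early. The safety set shows (10 − 10s)/(100 − 10s):

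- s = 25%: 7.5/97.5 = 7.7%
- s = 50%: 5/95 = 5.3%
- s = 75%: 2.5/92.5 = 2.7%

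The rate in the whole arm is 10% in each case.

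**4. Whether another stated set repairs this.** The per-protocol set requires a completed 3-month examination, so it does not bring back early stoppers who do not return for it. The separate account of dropouts lists numbers and reasons, not event rates by arm, and patients who stop the intervention for an event are not classed as withdrawn, so they may not appear there.

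**The case against.** Several counter-arguments have force.

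- *The events are not lost.* Correct. They are recorded in the case report form, and their type and frequency go to the national monitoring centre with no restriction to the FAS. A reader might infer that early stoppers' events disappear from the trial; the document does not support that. What is missing is their place in the analysed numerator and denominator.
- *The direction of the bias is not fixed.* Correct. A reader might infer that rates in A and B are necessarily too low. The second case under step 2 shows the opposite when early stoppers have fewer events than those who stay. Understatement is the expected result only where stopping is linked to events.
- *Group C was surely meant to be included.* Probably so. The primary and secondary outcomes compare three groups, and an FAS without controls would make the primary comparison impossible. The loss of Group C comes from the FAS sentence, and correcting that sentence would restore it. It should not be counted as a second, independent safety defect. The exclusion of early stoppers in A and B remains after that correction.
- *To include is not to equal.* Possible, but no other members are named and additional analyses are ruled out, so equality with the FAS is the natural reading.
- *The intervention is low risk.* The article says so: "There will be no data monitoring committee for this study because the intervention in this study is considered a low-risk intervention". This lowers the practical impact. A reader might go further and infer that the restricted set will be used to confirm that judgement. Nothing in the document says so: low risk is given as a prior reason for having no committee.

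**Conclusion.** The point holds as an inconsistency in a stated definition. The safety set requires 4 weeks of digital intervention, while the sections on discontinuation and adverse events keep early stoppers under evaluation and record their events from the first day. On any reading in which the safety set is the FAS, patients in A and B who stop before 4 weeks are excluded for their whole follow-up. If they leave, they do not take with them the early events of patients who continue, so it would be wrong to describe the loss as a fixed portion of the study period.

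The size depends on an early-stopping rate that the document does not give. For 5% to 20% early stopping it is 10 to 40 of the 200 patients in A and B, plus all of Group C (about 100) if the FAS sentence is applied literally. In the assumed illustration the reported rate is 6.7% against 10%; under other assumptions it could be slightly too high. The supportable statement is that the set can understate harm, not that it must.

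**What to change.** Define the safety population separately from the FAS: all randomised participants in all three arms, with no minimum exposure. Summarise adverse events from day 1 by arm; events between consent and day 1 can be listed apart, in line with the existing pre-existing-condition rule. Reconcile the analysis-set paragraph with the discontinuation and adverse event sections, so that a patient who stops because of an event is visibly kept in both numerator and denominator. The FAS sentence should also be corrected so that it does not exclude Group C.

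The cost is about one sentence for the safety set. No new data are needed, because the adverse event section already requires them. The change should be made before the analysis, since redefining the set once results are known would be open to challenge.
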